
#### Ethics

This study is conducted in accordance with the principles of the Declaration of Helsinki and 'good clinical practice' guidelines. The independent medical ethics committees of the participating centers have approved the study protocol. Written informed consent is obtained prior to randomization; consent by proxy will be obtained for patients who are temporally unable to provide consent.

### Statistical analysis

#### Sample size

From previous studies the clinical cure rate is estimated to be approximately 90% [9,10,21]. This study will have power of 90% to show that the clinical cure rate for Short treatment (7 days followed by placebo for 7 days) is at least as high as the cure rate for Standard treatment (14 days). Assuming that the event rates for the Standard treatment and Short treatment populations are 90% and 89.5%, respectively, that a difference of 10,0 points or less is unimportant, and that alpha (1 tailed) is set at 0.05, the sample size in the two groups will be 200 each. Formally, the null hypothesis is that the clinical cure rate for Short treatment is 10,0 percentage points lower than the cure rate for Standard treatment, and the study has power of 90% to reject this null. Equivalently, the likelihood is 90% that the 95,0% confidence interval (CI) for the difference in clinical cure rates will exclude a 10,0 point difference in favor of Standard treatment. We adopted 10% as the margin of non-inferiority as suggested previously [22]. In order to evaluate 200 patients in both treatment arms and considering subjects who will discontinue the study for various reasons, we estimate that 480 patients are needed to be randomized and 580 patients must be screened for randomization. According to CONSORT the flow of expected participants are outlined in Figure 2[23].

**Figure 2 F2:**
[figure not shown]
**Recruitment of consecutive patients with acute pyelonephritis**.

#### Intention to treat, per-protocol and subgroup analysis

The primary endpoint will be analyzed on the Intent-To-Treat population, including all randomized patients who received at least one dose of the study drug, and on the Per-Protocol population, including all randomized patients who had been given the study drug for a minimum of 24 hours (in case of treatment failure) or who had been taken at least 80% of the study drug (in case of clinical cure). The primary significance test will be carried out on the equivalence in cure rates or clinical failure rates in the two treatment arms.

Descriptive statistics will be used to describe the baseline characteristics of the participants in each arm. Binomial or categorical outcome measures will be analyzed using Chi-square tests (Pearson's or Fisher's). Risk difference with 95% CI will be used to compare the differences of categorical outcomes. The primary outcome variable is clinical cure rate assessed 10- to 18 days post-treatment. As we are only interested in non-inferiority and not in equivalence, the sample size calculation is based on a one-tailed alpha of 0.05. This implies that the 90% CI of a two-tailed Chi-square test should not cross the predefined risk difference of 10% lower clinical cure rate [24].

The primary outcome will additionally been tested in the subgroups of males, females, patients with acute complicated pyelonephritis, patients with any co-morbidity, patients aged ≥ 50 years, patients with bacteremic UTI and patients with stepdown treatment (antimicrobials intravenously followed by oral ciprofloxacin during the first 7 days). Subgroup analysis and all secondary outcome measures will be analyzed using Chi-square tests.

In case of significant differences in baseline characteristics, which may have happen by chance as we only stratify randomization by sex and center, the primary outcome will additionally be tested using a multivariable binary logistic regression model to adjust for the following potential confounders: age, acute complicated pyelonephritis, underlying co-morbidity and the use of stepdown treatment.

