#### Definitions

The following definitions will be used. *Clinical cure *is defined as being alive with the absence of fever (temperature < 38.0°C) and the resolution of UTI symptoms (either absence of symptoms or at least 2 points improvement on a 0 through 5 points severity score) through the post-treatment visit whereas no additional antimicrobial therapy for a relapse of UTI is described. *Clinical treatment failure *is the opposite of clinical cure and defined as deterioration, persistent fever and/or symptoms of UTI (less than 2 points improvement on a 0 through 5 points severity score) or relapse of UTI with the same uropathogen for which additional antimicrobial treatment is prescribed. *Clinical recurrence *is defined as any clinical UTI after clinical recovery and the end of treatment period including uncomplicated UTI, complicated UTI and acute pyelonephritis as defined previously [19]. Based on microbiological typing of isolated uropathogen distinction will be made between clinical relapse, being the same uropathogen or clinical reinfection with a different uropathogen. *Pre-treatment significant growth of uropathogens *is defined as ≥ 10^4 ^colony forming units/mL in women (midstream urine) or ≥ 10^3 ^colony-forming units/mL in men (midstream urine) or ≥ 10^3 ^colony-forming units/mL (catheter urine) or ≥ 10^2 ^colony-forming units/mL of midstream urine collected during antibiotic treatment of UTI at study entry [19]. *Bacteriologic cure *or eradication is defined as the elimination of the study entry uropathogen or as pathogen growth of less than 10^4 ^colony forming units/mL in women or less than 10^3 ^colony-forming units/mL in men, of a midstream urine sample collected combined with the disappearance of leucocyturia [19]. *Bacteriologic failure *through the 10- to 18-day post-treatment visit is defined as the absence of bacteriologic cure and classified as persistence of the original pathogen or superinfection with a new pathogen on the basis of species determination and antibiogram or an alternative method, such as Amplified Fragment Length Polymorphism or sequence-based PCR using repetitive extragenic palindromic primers. *Ciprofloxacin resistance *of uropathogens is defined by a MIC > 4 mg/L and includes all *Enterococcus spp. Acute complicated pyelonephritis *is defined as febrile urinary tract infection in a person with one or more of the following baseline characteristics: male sex, postmenopausal (female aged ≥ 50 years), underlying urinary tract disorder (e.g. nephrolithiasis, urologic malignancy, vesicoureteral reflux, urethral stricture), diabetes mellitus, immunocompromised, renal insufficiency or progressive UTI despite antimicrobial UTI treatment. *Co-morbidity *is defined as the presence of any urinary tract disorder, heart failure, cerebrovascular disease, renal insufficiency, diabetes mellitus, malignancy or chronic obstructive pulmonary disease for which the patient is prescribed medication and/or consults a hospital-based medical specialist.

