In contrast to previous studies, the current study includes consecutive patients with febrile UTI, being AP, reflecting the daily clinical practice of primary care and emergency departments. This includes male participants who by definition are classified as complicated. This might be controversial but from a pathophysiological point of view there is no reason to believe that AP in men behaves different from AP in women. Indeed, previous studies that included a sufficient number of men, showed that treatment of febrile UTI with fluoroquinolones for 7–14 days had comparable clinical cure rates of about 90% [28,30-32]. Moreover, we recently evaluated the guideline of the Dutch College of General Practitioners that recommends antimicrobial treatment of febrile UTI for 10 days irrespective of sex [33]. In this observational study with similar inclusion criteria, male sex was not a risk factor for clinical failure [21]. As in previous studies, the mortality rate in men was higher but this reflects underlying co-morbidity rather than attributable risk of UTI [5,21]. Based on the results of these studies we conclude there is sufficient evidence to include men in such a trial as this. Furthermore, it should be emphasized that although men with suspected chronic bacterial prostatitis are excluded from this trial it might be that men with febrile UTI have indeed acute prostatitis. However, as recommended treatment durations of acute prostatitis are primarily based on expert opinion (being 14 days) and the distinction of febrile UTI in men between pyelonephritis or prostatitis can often not be made clinically, a trial evaluating the optimal treatment duration is even more relevant in this population [34].

In contrast to all previous studies, the study objective of this trial only involves treatment duration. Combined with the inclusion of patients reflecting routine daily practice these aspects are thus unique that it is named with the acronym FUTIRST (Febrile UTI Randomized Short Treatment)-trial to put emphasis on being the first clinical trial on febrile UTI or AP with such a pragmatic design. Meeting the criteria for a practical clinical trial, the results of this study are thus generalizable to other settings and should influence policy makers of treatment guidelines on AP [35].

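### The Per-Protocol rule counts as 7-day cures those Short-arm patients who took another active antibacterial for a non-UTI infection during the placebo week

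*Protocol article*

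**What the plan says.** The section on intention to treat, per-protocol and subgroup analysis sets two routes into the Per-Protocol set. A treatment failure enters if the patient is one "who had been given the study drug for a minimum of 24 hours (in case of treatment failure"). A cure enters under the clause "or who had been taken at least 80% of the study drug (in case of clinical cure"). The ITT set is wider still, "including all randomized patients who received at least one dose of the study drug". None of these rules refers to antibacterials other than study drug.

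The Definitions section attaches an antibiotic condition to the outcome, but a narrow one. Clinical cure requires survival, no fever and resolution of UTI symptoms through the post-treatment visit, "whereas no additional antimicrobial therapy for a relapse of UTI is described". On the failure side, the antibiotic clause is "relapse of UTI with the same uropathogen for which additional antimicrobial treatment is prescribed". A course given for any other infection affects neither definition.

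The Treatment section sets the contrast: 7 days of active drug followed by 7 days of placebo, against 14 days of active drug. The Discussion says that "the study objective of this trial only involves treatment duration".

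**The concern.** A Per-Protocol set in a duration trial should compare patients who received roughly the assigned durations of active treatment. Here a Short-arm patient can take all the placebo tablets, receive an outside antibacterial that covers uropathogens during days 8-14, and still count as a success of the 7-day regimen. In the Standard arm the same course adds little, because the patient is already on ciprofloxacin. In the Short arm it stands in for the withheld week. In a non-inferiority trial, anything that makes the arms more alike favours the claim.

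The usual safeguard is to compare the ITT and Per-Protocol results. It does not help here, because both sets keep these patients and agreement between them says nothing about this source of dilution.

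The setting makes such use plausible. The trial deliberately includes elderly and co-morbid patients, and its co-morbidity definition lists "malignancy or chronic obstructive pulmonary disease for which the patient is prescribed medication". That text shows who is enrolled. It gives no rate of antibiotic use.

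**Working it through.** **Inputs (protocol article, Sample size and analysis sections).** Standard cure 90%, Short cure 89.5%, margin 10 points, one-tailed alpha 0.05, power 90%, 200 evaluable per arm, 480 randomized. The analysis section judges non-inferiority by a 90% confidence interval.

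**The plan's own figure.** With d = 0.10 − 0.005 = 0.095:

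n = (0.90×0.10 + 0.895×0.105) × (1.645 + 1.282)² / 0.095² = 174.6, so 175 per arm.

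With the continuity correction n/4 × (1 + √(1 + 4/(n·d)))², this becomes 195.1, so 196, which is within 3% of 200. I take 200 per arm as the base. The randomized total fits a loss of one in six: 400/(1 − 1/6) = 480.

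**Which patients pass the stated rules.** Take a Short-arm patient who took at least 80% of the placebo and received an outside antibacterial for a non-UTI infection on some of days 8-14.
- Per-Protocol route for cures: satisfied, since only tablet intake is examined.
- Antibiotic clause of clinical cure: satisfied, since the course was not for a UTI relapse.
- Fever clause: satisfied only if there was no fever through the visit. A febrile episode from the other infection would, read literally, prevent cure.

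The gap is therefore real, but limited to patients who remain afebrile.

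**Size, placebo week.** The share s of the Short arm affected is an assumption. Place the truth at the margin (Standard 90%, Short 80% without outside drug) and let affected patients be cured at 90%, so that the missing week is fully replaced.

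Short cure p = 0.90 − 0.10(1 − s); visible deficit D = 0.10(1 − s)

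SE = √[(0.90×0.10 + p(1 − p))/200]

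P(claim) ≈ Φ((0.10 − D)/SE − 1.645)

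| s (patients of 200) | p | D | SE | Normal approximation | Exact binomial, 90% CI | Exact binomial, 95% CI |
|---|---|---|---|---|---|---|
| 0 (0) | 0.800 | 0.100 | 0.0354 | 5.0% | 5.3% | 2.7% |
| 2% (4) | 0.802 | 0.098 | 0.0353 | 5.6% | 5.9% | 3.1% |
| 5% (10) | 0.805 | 0.095 | 0.0351 | 6.6% | 7.0% | 3.7% |

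The exact columns sum over all pairs of binomial outcomes, using the unpooled Wald interval. Partial activity scales s: a drug that restores half the missing benefit in 4% of patients has the effect of s = 2%.

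**After day 14.** The post-treatment visit falls at about day 24 to 32 (14 + 10 to 14 + 18). From day 15 neither arm is on study drug, so outside courses can occur equally in both. If a share f in each arm is treated and all of them are cured, the difference is [0.90(1 − f) + f] − [0.80(1 − f) + f] = 0.10(1 − f). The difference still shrinks, but symmetrically and not because a withheld week has been replaced.

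**Cost of excluding.** Power = Φ(0.095/SE − 1.645), with SE = √(0.183975/n). At n = 200 it is 0.932; at n = 196 (2% excluded) 0.927; at n = 190 (5% excluded) 0.92.

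**The case against.** The best objection is that the article is condensed. It gives exposure thresholds without saying that they are the only Per-Protocol criteria, and concomitant medication is often handled in a full protocol or SAP that is not shown. That limits the point but does not remove it. The article does state a membership rule, and that rule admits these patients. If another document narrows it, the two need to agree.

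Three further objections stand and set the limits of the point.
- A reader might infer that the bias is one-sided over the whole period to the visit. The replacement argument holds only for days 8-14; later use is open to both arms.
- A reader might picture a febrile chest infection counted as a cure. The definition requires absence of fever through the visit, not only at it, so such a patient is not literally a cure. If febrile infections were commoner on placebo, this would work against non-inferiority.
- The size depends on an assumed rate. At 2% it is small, and nothing in the document supports a much higher share.

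The article also stresses a pragmatic design, in which incidental antibiotics are part of practice. That is a reason to keep these patients in the ITT set. It does not justify counting them as per-protocol recipients of 7 days.

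**Conclusion.** The point holds in a limited form. The stated Per-Protocol rule and the cure definition together let a Short-arm patient with outside active treatment in the placebo week, afebrile throughout, count as a 7-day cure. The direction is toward non-inferiority. This is an inference from the design, since the documents do not measure it. Assuming 2% to 5% of the Short arm, full replacement of the missing week and a true deficit exactly at the margin, the false non-inferiority rate goes from about 5.3% to 5.9%-7.0% under the 90% interval rule. This is a modest effect that is cheap to prevent.

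It would be tempting to extend the point to bacteriologic cure, because the plan uses a lower growth threshold for "midstream urine collected during antibiotic treatment of UTI at study entry" and has no counterpart at follow-up. The documents do not support that. The entry threshold serves diagnosis, bacteriologic cure also requires leucocyturia to disappear, and the Per-Protocol analysis is described for the primary endpoint only.

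**What to change.** Add a criterion to the Per-Protocol definition in the section on intention to treat, per-protocol and subgroup analysis, worded identically for both arms and applied blind to allocation:

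- Patients who received a non-study systemic antibacterial with activity against uropathogens, for an indication other than UTI, between the start of blinded study medication and the post-treatment visit are not counted as per-protocol cures and leave the Per-Protocol set.
- Patients who had already met clinical treatment failure stay in the set as failures, so that the exclusion does not remove failures under a non-UTI label.
- All of these patients stay in the ITT set as observed, and the number affected is reported per arm.

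The case record form must capture drug, indication and dates of concomitant antibacterials at the existing contacts. No extra visits or patients are needed. The cost is a slightly smaller Per-Protocol set, with power about 0.93 falling to 0.92 if 5% are excluded.

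### The primary non-inferiority rule is given once as a 95% and once as a 90% confidence interval; at 200 per arm the stated 90% power fits the 90% interval, not a two-sided 95% one

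*Protocol article*

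**What the plan says.** The Sample size section of the Protocol article gives the design inputs: "Assuming that the event rates for the Standard treatment and Short treatment populations are 90% and 89.5%, respectively", a margin of 10 points, and "alpha (1 tailed) is set at 0.05, the sample size in the two groups will be 200 each". It places the null hypothesis at a 10-point deficit for Short and claims that "the study has power of 90% to reject this null". It then offers what it presents as an equivalent form: "the likelihood is 90% that the 95,0% confidence interval (CI) for the difference in clinical cure rates will exclude a 10,0 point difference" in favour of Standard. Nothing there says whether that interval is one-sided or two-sided.

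The section on intention-to-treat, per-protocol and subgroup analysis repeats the alpha: "As we are only interested in non-inferiority and not in equivalence, the sample size calculation is based on a one-tailed alpha of 0.05". The only sentence worded as a success criterion follows from it: "This implies that the 90% CI of a two-tailed Chi-square test should not cross the predefined risk difference of 10% lower clinical cure rate".

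Two other sentences of the same section bear on the rule. One covers categorical outcomes in general: "Risk difference with 95% CI will be used to compare the differences of categorical outcomes". The other comes earlier: "The primary significance test will be carried out on the equivalence in cure rates or clinical failure rates in the two treatment arms".

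**The concern.** An unqualified 95% interval is normally read as two-sided, and its lower limit then tests at a one-sided 2.5%. The lower limit of a two-sided 90% interval tests at a one-sided 5%. The article derives both intervals from the same one-sided 5%, so one of the two sentences is wrong unless the 95% interval is meant to be one-sided.

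The trial's single confirmatory conclusion rests on this rule. For a result near the margin, the sentence that the analyst follows decides whether 7 days is declared non-inferior.

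Two points of wording add to the doubt. Equivalence is named as the object of the primary test and then ruled out. A chi-square test is named as the source of the interval, although its usual null is a difference of zero, not the 10-point deficit that the Sample size section states.

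**Working it through.** **Inputs (Sample size section).** Standard 90%, Short 89.5%, margin 10 points, 200 evaluable per arm, one-sided alpha 0.05, power 90%. The article names no formula and no interval type, so the variants below are assumptions.

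**Step 1. Reproduce the plan's figure at one-sided 5%.**
- The sum of the variances is 0.895 × 0.105 + 0.9 × 0.1 = 0.183975. The distance from the assumed difference to the margin is 0.10 − 0.005 = 0.095.
- Unpooled: n = 0.183975 × (1.645 + 1.282)² / 0.095² = 174.6, so 175 per arm.
- With a continuity correction: n′ = (n/4) × [1 + √(1 + 4/(0.095n))]² = 195.1, so 196 per arm.
- Farrington-Manning null variance: 187 per arm.

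The continuity-corrected figure is close to the stated 200, so the plan's sample size reproduces at one-sided 5%.

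**Step 2. Power at 200 per arm under each rule.** SE = √(0.183975/200) = 0.0303.
- Unpooled: Φ(0.095/0.0303 − z).
- Continuity-corrected: Φ((0.095 − 1/200)/0.0303 − z).
- Farrington-Manning: Φ((0.095√200 − z·s₀)/s₁), with s₁ = √0.183975 and s₀ taken at the constrained null rates of 83.0% (Short) and 93.0% (Standard).

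| Formula | 90% CI (z = 1.645) | two-sided 95% CI (z = 1.960) |
|---|---|---|
| Unpooled | 93.2% | 87.9% |
| Farrington-Manning | 91.8% | 85.5% |
| Continuity-corrected | 90.7% | 84.3% |

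For 90% power, a two-sided 95% interval would need 215, 230 or 235 per arm in the same order.

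Two less usual variants give the same ordering. With the null variance fixed at 90% and 80%, power is 88.8% and 80.2%. With two one-sided tests (a true equivalence test), it is 89.7% and 81.3%. In both, the stated 90% lies near the 90% interval and well above the two-sided 95% interval.

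**Step 3. Can the same data pass one rule and fail the other?** Take Standard at 180/200 and the simple (Wald) interval for Short minus Standard, d ± z × √[(p_S(1−p_S) + 0.09)/200].

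| Short cured | Difference (points) | Lower limit, 90% CI | Lower limit, 95% CI |
|---|---|---|---|
| 170/200 | −5.0 | −10.42 | −11.46 |
| 171/200 | −4.5 | −9.88 | −10.91 |
| 172/200 | −4.0 | −9.34 | −10.36 |
| 173/200 | −3.5 | −8.79 | −9.80 |

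At 171 and 172 the two rules disagree.

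**Step 4. How often?** Exact enumeration of the two binomials at 90% v 89.5% gives success in 92.9% (90% CI) and 88.0% (95% CI) of trials. The 95% interval contains the 90% one, so the difference, about 5%, is the share of split results. With a Newcombe interval it is 92.5% − 86.7% = 5.8%. If the true Short rate were 86%, which is not a planning assumption, about 12% of trials would split (Wald).

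**Step 5. Error at the margin.** At a true 90% v 80%, the exact Wald rule declares non-inferiority in 5.3% (90% CI) and 2.7% (95% CI) of trials.

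**The case against.** The strongest reply is that the article largely settles the rule. It states one-sided 0.05 in both sections, and only one sentence, the one with the 90% interval, is worded as a criterion for success. The 95% sentence in the Sample size section is a gloss on power. If it means a one-sided 95% interval, its lower limit is that of the two-sided 90% interval and the sections agree. This is probably what was meant, and it shows which sentence to correct. It does not remove the defect: the text does not say one-sided, and the analysis section uses 95% again for risk differences without qualification.

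That second 95% sentence is weaker evidence of conflict. It is a general reporting statement, and a descriptive 95% interval can stand beside a decision made at one-sided 5%. The equivalence sentence is loose wording: the null hypothesis and margin run in one direction only and no upper margin is given, so no equivalence test is actually specified. The choice of interval method is detail that a condensed article may leave to the full plan. These replies stand, and these items are secondary.

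A reader might infer from the unpooled figures (93% and 88%) that the stated 90% power matches neither rule and that 200 per arm is a wrong number. The documents do not support that. They name no formula, and with a continuity correction the stated size reproduces at one-sided 5%.

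It may also be said that the power shortfall vanishes if all 480 randomized patients are analyzed: at 240 per arm the continuity-corrected power is 94.9% and 90.7%. But the article states its 90% for 200 per arm and adds the rest to cover losses.

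**Conclusion.** The point holds as an inconsistency in the primary decision rule. As two-sided intervals, the 95% and 90% versions differ in one-sided error (2.5% v 5%) and give opposite conclusions for some results, in about 5% of trials at the planning assumptions. The claim that the two forms are equivalent is false unless the 95% interval is one-sided. The sample size is not at fault: at 200 per arm the three usual formulas give about 91% to 93% under the 90% interval, against about 84% to 88% under a two-sided 95% interval.

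A reader might go further and conclude that the two-sided 95% interval should govern. The documents point the other way, since the alpha stated in both sections, the explicit criterion and the sample size all agree with the 90% interval.

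The power range depends on the unnamed formula, and the counts in the example on the Wald interval. Another interval type may shift the counts, but a 95% interval remains wider than a 90% one.

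The correction should be made before unblinding, because it concerns the trial's only confirmatory threshold.

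**What to change.** State one rule, in the same words, in both sections: Short is non-inferior if the lower limit of the two-sided 90% confidence interval (equal to a one-sided 95% lower bound) for the risk difference in clinical cure, Short minus Standard, lies above −10 percentage points. Then:
- correct the 95% interval in the Sample size section to match;
- say that any 95% interval reported for the primary outcome is descriptive;
- replace equivalence with non-inferiority in the sentence on the primary test;
- describe the primary analysis as a risk-difference interval compared with the margin, not a chi-square test, and name the interval method.

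This costs wording only and leaves the sample size and stated power unchanged.

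If the sponsor prefers a two-sided 95% interval, use it in both sections and restate the power at 200 per arm as about 84% to 88%, with the figure matched to the chosen method. Keeping 90% power under that rule would instead need 215 to 235 evaluable patients per arm.

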## Methods/Design

A randomized placebo-controlled double-blind multicenter trial is conducted with the aim to determine non-inferiority of the primary outcome measure between short treatment and standard treatment of febrile UTI. Consecutive patients will be randomized in a 1:1 ratio stratified per center and sex, to receive either a 7-day or 14-day regimen of antimicrobial treatment. Those enrolled in the 7-day regimen will be provided with placebo tablets to match antimicrobial tablets to complete a 14-day course.

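### Centre and sex stratify the randomisation but enter neither the primary comparison nor the adjusted model, adjustment hangs on baseline significance tests, and the logistic and subgroup tests do not by themselves address the 10-point margin

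*Protocol article*

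**What the plan says.** Under Methods/Design, patients are "randomized in a 1:1 ratio stratified per center and sex". The Randomization section gives eight centre levels (seven hospitals, with all primary care as one), each split by sex.

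Under Intention to treat, per-protocol and subgroup analysis, the primary decision compares the 90% confidence interval for the difference in cure rates with a 10-point deficit. No stratification of that comparison is mentioned. The margin itself is on the risk-difference scale: "We adopted 10% as the margin of non-inferiority as suggested previously".

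The same section makes covariate adjustment conditional: "In case of significant differences in baseline characteristics, which may have happen by chance as we only stratify randomization by sex and center", then "the primary outcome will additionally be tested using a multivariable binary logistic regression model". The model has four fixed covariates: age, acute complicated pyelonephritis, co-morbidity and stepdown treatment. Centre and sex are not listed. Sex enters only indirectly, because male sex is one of several criteria for complicated pyelonephritis under Definitions.

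For subgroups the section states: "Subgroup analysis and all secondary outcome measures will be analyzed using Chi-square tests". Seven subgroups are named and no interaction test is mentioned. A general sentence in the section promises a risk difference with 95% confidence interval for categorical outcomes.

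**The concern.** There are four linked weaknesses, all in rules that the text states rather than leaves open.

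- **Stratification.** The factors used to balance the arms are normally carried into the analysis. Without them the standard error tends to be slightly too large. Centre appears nowhere in the analysis, although it separates primary care from the hospitals that receive patients judged ill enough for admission.
- **Trigger.** A significance test on a baseline variable in a randomised trial tests a hypothesis known to be true. It does not measure prognostic importance: a non-significant imbalance in a strong predictor can matter more than a significant one in a weak predictor. Trigger and remedy also do not match, since an imbalance in any characteristic leads to the same four covariates.
- **Scale.** A logistic model by default tests an odds ratio of 1, whereas the trial's question is a difference of 10 percentage points.
- **Subgroups.** A chi-square test within a subgroup asks whether the difference is zero. In a small subgroup a deficit as large as the margin will often be non-significant. Men, older patients and patients with co-morbidity are the groups that the article presents as new compared with earlier trials.

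At stake is whether the supportive results can inform the non-inferiority question, and whether they exist for reasons fixed in advance.

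**Working it through.** **Inputs from the Sample size section.** "Assuming that the event rates for the Standard treatment and Short treatment populations are 90% and 89.5%, respectively"; "alpha (1 tailed) is set at 0.05, the sample size in the two groups will be 200 each"; "the study has power of 90% to reject this null"; margin 10 points.

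**The plan's own figure.** n = [pc(1-pc) + pt(1-pt)] × (z0.95 + z0.90)² / (0.10 - 0.005)² = (0.0900 + 0.0940) × 8.564 / 0.009025 = 174.6, so 175 per arm. A continuity correction, n/4 × [1 + √(1 + 4/(n × 0.095))]², gives 196, within 3% of the stated 200. Power at 200 per arm without the correction is 93.2%. The design figure is sound and nothing below changes it.

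**Trigger.** The chance of at least one p < 0.05 among k independent baseline tests under sound randomisation is 1 - 0.95^k. The article does not give k.

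- k = 4 (the listed covariates): 18.5%
- k = 10: 40.1%
- k = 20: 64.2%

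Correlated characteristics would lower these figures.

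**Margin as an odds ratio.** OR = [(p - 0.10)/(1.10 - p)] / [p/(1 - p)], with p the control cure rate.

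- p = 95%: (0.85/0.15)/(0.95/0.05) = 0.298
- p = 90%: (0.80/0.20)/(0.90/0.10) = 0.444
- p = 85%: (0.75/0.25)/(0.85/0.15) = 0.529
- p = 80%: (0.70/0.30)/(0.80/0.20) = 0.583

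Conversely, holding OR at 0.444 would tolerate a loss of 5.6 points at 95% control cure, 13.4 at 85% and 16.0 at 80%. No single odds-ratio margin stands in for 10 points.

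**Stratifying by sex.** Assume 40% men, 200 per arm, an overall control cure of 90% and a true deficit of 10 points in each sex. In 200,000 simulated trials per scenario, type I error (nominal 0.05) and the reduction in standard error were:

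- cure 90% in both sexes: 0.052 unstratified, 0.052 stratified; SE 0.3% lower
- men 86%, women 92.7%: 0.052 and 0.053; SE 0.7% lower
- men 82%, women 95.3%: 0.049 and 0.053; SE 2.0% lower

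An analytic check of the last scenario: the per-patient variance summed over arms is 0.90 × 0.10 + 0.80 × 0.20 = 0.25. Stratifying removes 2 × 0.40 × 0.60 × 0.133² = 0.0085, or 3.4% of the variance and about 1.7% of the SE. The 0.3% where sex has no effect is a finite-sample artefact. Centre was not simulated because the article gives no centre-specific rates.

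**Subgroups.** Power to exclude a 10-point deficit (90% v 89.5%, one-sided 0.05) is Φ(0.095/√(0.184/n) - 1.645). For assumed subgroup shares of 50%, 40%, 25% and 20% of the 200 per arm, it is 72%, 63%, 47% and 40%. With an assumed 60 per arm, a two-sided 5% chi-square test has 33% power for 80% v 90%, so a deficit equal to the margin is non-significant about two times in three.

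**Room for adjustment.** Expected failures are 200 × 0.10 + 200 × 0.105 = 41. A model with arm, sex, seven centre terms and the four listed covariates has 13 terms, or 41/13 = 3.2 failures per term. Reducing centre to one term leaves 7 terms, or 41/7 = 5.9.

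**The case against.** The strongest reply is that the trial's conclusion rests on the unadjusted risk difference, that the logistic model and subgroup tests are additional, and that the measurable loss from leaving out sex is slight. All of that stands. The fixed covariate list also limits data-driven choice, which is to the plan's credit.

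Several stronger readings are tempting and the article does not support them.

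- A reader might infer that the adjusted result will be reported as an odds ratio. The text names a logistic test but no effect measure, and a marginal risk difference can be derived from such a model. The sound criticism is only that a logistic test does not by itself answer the margin question.
- A reader might infer that no subgroup result can be read against the margin. The general promise of a risk difference with 95% interval can cover clinical cure within subgroups. What remains is the test named for subgroups and the absence of an interaction test.
- A reader might infer that non-significance in, say, men would be taken as non-inferiority. Nothing says so; non-inferiority is defined by an interval against the margin.
- To say that stratification is ignored goes too far: it is used in allocation, sex is part of one covariate, and males and females are named subgroups. But that covariate also takes in women aged 50 or over and patients with diabetes, so it does not adjust for sex.
- A false-positive chance of 30% for seven subgroup tests (1 - 0.95^7) assumes independence. The subgroups overlap: by definition every man and every woman aged 50 or over has complicated disease.

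An analysis plan not shown may refine these points, but the published text commits to the trigger, the covariate list and the subgroup test.

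**Conclusion.** The point holds as a recommended improvement to how the analyses are specified. The primary non-inferiority conclusion is not invalidated as written.

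From the text alone: the primary comparison and the adjusted model both leave out the stratification factors, adjustment depends on baseline significance tests, and subgroup chi-square tests address zero difference rather than the margin or interaction.

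The sizes rest on assumptions. The trigger fires by chance in about 19% of trials with 4 tests and 40% with 10, if the tests are independent and their number is as assumed. The margin corresponds to odds ratios of 0.30 to 0.58 for control cure of 95% to 80%. Stratifying by sex lowers the SE by about 0.3% to 2% and moves type I error by at most about 0.4 points, with the unstratified analysis on the conservative side, if 40% are men. The effect of centre is not quantified. The case for change is therefore mainly prespecification and interpretability, with only a small precision gain shown.

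**What to change.** 1. Estimate the risk difference in clinical cure stratified by sex and centre (Mantel-Haenszel, with small hospitals pooled by a rule set before unblinding), and read its confidence interval against -10 points. The interval level needs settling separately, since the Sample size section refers to 95% and the analysis section to 90%.
2. Delete the baseline-significance trigger.
3. If a covariate-adjusted analysis is kept, always run it, with a short prespecified set: sex, pooled centre and the four listed covariates. All centre levels should not be fitted separately with about 41 expected failures. Report the result as a marginal risk difference with its interval.
4. For subgroups, state explicitly that the risk difference with interval already promised for categorical outcomes applies, add a treatment-by-subgroup interaction test, and label the results exploratory.

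The cost is a few sentences in the analysis text and a little more programming. No new data are needed and the sample size does not change.
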